**Trial registration number:**

ClinicalTrials.gov under NCT03249623. This research is registered with the National Institute for Health Research under CPMS ID: 34831.

Strengths and limitations of this studySingle-blinded multicentre randomised control trial evaluating management of mechanical ventilation as directed by the BEACON Caresystem compared with that of standard care in the general intensive care setting.The BEACON Caresystem is a model-based decision support system that uses mathematical models of patients’ physiology in combination with models of clinical preferences to provide advice on appropriate ventilator settings.Sample size was determined by a power analysis of the duration of mechanical ventilation.Patients and the public were not involved in the design of this study.The study does not assess successful rehabilitation of the patient subsequent to their intensive care unit stay.

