#### Spontaneous breathing trial (SBT)

During weaning from mechanical ventilation, the BEACON Caresystem monitors the levels of Pressure Support (PS) and Positive End Expiratory Pressure (PEEP). When these levels are reduced to values below clinical guideline thresholds,^21^ the BEACON Caresystem automatically monitors variables evaluating spontaneous breathing criteria. If these remain within limits and for a duration determined by international guidelines,^21^ the system prompts the user to assess the appropriateness of extubation and provides a checklist to help. The primary function of the BEACON Caresystem with regards weaning is to reduce levels of support where possible; it does not suggest an active SBT or extubation. As such, the decision to extubate is according to standard clinical practice for both arms of the study, meaning that at any time the clinical team can perform an active SBT or extubate the patient without confirmation from the system. Reintubation is documented by the research team and the participant enters a standard care pathway, which involves the deactivation of the BEACON Caresystem. The participant is then followed up until the end of the protocol (figure 1).

The protocol ends with transfer or discharge from ICU or death (figure 1).

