Duration of mechanical ventilation to successful extubation following randomisation defined as the time from randomisation and until successful extubation, with successful extubation defined as ≥48 hours of unassisted spontaneous breathing after extubation.Time from control mode to support mode defined as the time following randomisation, from initiation of control modes of ventilation and until initiation of support modes of ventilation.Time from support mode to successful extubation defined as the time following randomisation, from initiation of support modes of ventilation and until successful extubation.Number of changes in ventilator settings per day defined as the daily registered number of changes to ventilator settings from randomisation until successful extubation.Time to first SBT defined as the time from randomisation to the first performed SBT.Time to first successful SBT defined as the time from randomisation to the first successful SBT.Time to first extubation defined as the time from randomisation to the first extubation attempt.Time to first disconnection from mechanical ventilation defined as the time from randomisation to the point at which mechanical ventilation is first discontinued.Percentage of time in control mode ventilation defined as the time from randomisation which is spent in controlled modes of mechanical ventilation in per cent of duration of mechanical ventilation.Percentage of time in support mode ventilation defined as the time from randomisation which is spent in support modes of mechanical ventilation in per cent of duration of mechanical ventilation.Use of sedatives defined as the cumulative use of sedative drugs from randomisation until successful extubation.Use of neuromuscular blockading agents defined as the cumulative use of neuromuscular blockading agents from randomisation until successful extubation.Number of intubation free days defined as the number of days without intubation from randomisation until successful extubation.Number of reintubations defined as the number of reintubations following extubation from randomisation until successful extubation.Number of tracheostomies defined as the number of patients having tracheostomy performed from randomisation until successful extubation or protocol end.Number of patients on prolonged mechanical ventilation defined as the number of patients on mechanical ventilation ongoing for more than 21 days after the start of mechanical ventilation.Number and types of adverse events related to mechanical ventilation defined as the incidence of adverse events directly related to mechanical ventilation.ICU mortality defined as the mortality from randomisation and until death or ICU discharge.Length of stay defined as the duration of ICU admission from the start of mechanical ventilation and until death or ICU discharge.Mobilisation times defined as the time from randomisation until (1) first mobilisation, for example, sitting on the edge of the bed, standing up and marching on the spot and (2) regaining independency, for example, able to drink/eat or comb hair.Daily patient physiological blood gas status defined as daily ABG values of SaO_2_, PaO_2_, PaCO_2_, pH from randomisation until successful extubation.Daily average physiological status defined as daily averages of measured values of oxygenation (SpO_2_), end-tidal CO_2_ fraction (EtCO_2_), ventilation (respiratory rate, tidal volume, anatomical dead space), pulmonary mechanics (airway pressure, respiratory system compliance) and ventilator settings as measured routinely at the bedside.

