
### Statistical considerations

Sample size was determined by a power analysis of duration of mechanical ventilation. Extrapolation of the 2016 ICU admission data from two London-based NHS hospitals provided a sample size of 548 patients over an 18-month period. In these patients, mean total duration of mechanical ventilation measured in days was 7.2, with an SD of 7.0 days. A study population of 137 patients in each randomisation group would allow detection of a 2 day or 30% improvement in the duration of mechanical ventilation in the BEACON Caresystem group assuming a similar improvement in SD, with an α level of 0.05 and power of 0.8. A 2 days or 30% reduction in duration of mechanical ventilation is similar to that used previously.^6^

Primary and secondary outcomes will be measured across the protocol duration and comparison made by independent samples t-test, or appropriate non-parametric testing if not normally distributed. Complementary analysis will be performed using Kaplan-Meier curves.

The study is not sufficiently powered to allow subgroup analysis for the groups specified in the randomisation strategy.

An independent data safety monitoring committee will be established as part of the study, with this committee responsible for defining stopping criteria. Safety data will be looked at after the first 80 patients have been recruited, with an interim analysis performed following 50% recruitment.

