## Discussion

This paper presents the study protocol of single-blinded multicentre randomised control trial evaluating management of mechanical ventilation as directed by the BEACON Caresystem compared with that of standard care in the general intensive care setting. To test the hypothesis that following advice from the BEACON Caresystem will reduce time to successful extubation, patients are randomised to care including advice from the system, or standard care. In addition, as secondary outcomes, the study will investigate whether application of the advice changes the time spent in control ventilation modes, the number of changes made to the ventilator, the use of medication such as sedative or neuromuscular blocking agents, the changes in clinical procedures such as reintubation or tracheostomy and clinical and physiological status of the patient. Although not powered to detect differences between groups, it will also investigate the length of stay at the ICU and patient mortality.

This study is the next step in evaluation of the advice of the BEACON Caresystem. A large number of studies have been performed validating the physiological models included in the system, as summarised in,^9^ and studies of short duration have been performed evaluating the physiological response to application of advice.^14 15^ This use of the system over the whole duration of ICU stay allows for assessment of more meaningful clinical outcomes, relating to the time spent on mechanical ventilation. In addition, the study includes only patients intubated for a minimum of 24 hours, meaning that short-term postoperative patients who may have rather uncomplicated intubation periods are not included.

The study includes limitations. The study was powered on duration of mechanical ventilation rather than duration to successful ventilation, this being the historical data available during study design. The study is not powered to detect changes in mortality, and does not follow-up on the patients after transfer from the ICU. In the context of this study, successful extubation is defined as the lack of need for non-invasive ventilator support for 48 hours after extubation, rather than successful rehabilitation of the patient subsequent to their ICU stay.

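### Mobilisation and independence times are cut off at ICU exit, which may differ by arm, so the planned test on recorded times can be biased in either direction

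*Protocol article*

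**What the plan says.** The list under Primary and secondary outcomes includes "Mobilisation times defined as the time from randomisation until (1) first mobilisation". Its second component is "2) regaining independency, for example, able to drink/eat or comb hair". Neither component has a time horizon, and no value is given for a patient who leaves the ICU or dies first.

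The observation window is set elsewhere. The section on the spontaneous breathing trial states: "The protocol ends with transfer or discharge from ICU or death". Statistical considerations ties every outcome to that window and names the comparison: "Primary and secondary outcomes will be measured across the protocol duration and comparison made by independent samples t-test". The sentence continues with a non-parametric alternative for non-normal data, and the next sentence adds Kaplan-Meier curves as a complementary analysis. The Discussion confirms that the study "does not follow-up on the patients after transfer from the ICU".

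ICU length of stay and ICU mortality are themselves secondary outcomes, so the dates of exit and death are already collected.

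**The concern.** Regaining independence is a recovery milestone that some patients may reach only on the ward. Such a patient has no recorded time, because observation has already stopped. The recorded times are thus a selected subset, chosen by whether the milestone came before ICU exit.

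Selection of this kind matters for a comparison when exit timing differs by arm. The device is tested for earlier successful extubation, and ICU stay is listed as an outcome that might change with it. If stay changes, the two arms have different windows in which a milestone can be seen. A test on recorded times then mixes the effect on recovery with the effect on length of observation. A difference could be reported, in either direction, as a difference in speed of recovery.

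**Working it through.** The protocol gives no figure for these milestones, so there is none to reproduce. From the document come the window (ICU exit or death), the tests and the arm size (137). Everything else below is an assumption chosen to show scale. Exit is treated as a single time counted from randomisation, and death is not modelled separately.

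**Step 1: closed form.** Let milestone time T be exponential with mean m in both arms (no true effect), and exit time C be exponential with mean c, independent of T. Take c = 10 days (control) and 8 days (device). Then

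- mean recorded time: E[T | T < C] = 1/(1/m + 1/c)
- proportion with a recorded time: P(T < C) = (1/m)/(1/m + 1/c)

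| m (days) | Recorded mean, control v device | Difference | With a value, control v device |
|---|---|---|---|
| 6 | 3.75 v 3.43 | 0.32 | 62% v 57% |
| 12 | 5.45 v 4.80 | 0.65 | 45% v 40% |
| 20 | 6.67 v 5.71 | 0.95 | 33% v 29% |

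For m = 6: 1/(1/6 + 1/10) = 3.75 and 1/(1/6 + 1/8) = 3.43.

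**Step 2: a less restrictive model.** Milestone time is log-normal (log-scale SD 0.8), identical in both arms. Stay is log-normal with mean 10 v 8 days and coefficient of variation 1. The correlation r between the two (log scale) is varied. Means use 400,000 simulated patients per arm. Type I error is for a two-sided 5% t-test in 1,000 simulated trials of 137 per arm. All pairs are control v device.

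| Median (days) | r | Recorded mean | Type I | Mean if exit is entered as the end time | Type I | Kaplan-Meier proportion unrecovered at the median (truth 0.50) |
|---|---|---|---|---|---|---|
| 5 | 0 | 4.45 v 4.15 | 8.3% | 4.59 v 4.17 | 20.4% | 0.500 v 0.500 |
| 5 | 0.4 | 5.16 v 4.84 | 7.9% | 5.30 v 4.84 | 13.5% | 0.536 v 0.552 |
| 5 | 0.7 | 5.91 v 5.58 | 5.0% | 6.01 v 5.54 | 9.9% | 0.557 v 0.591 |
| 8 | 0 | 6.12 v 5.67 | 8.7% | 5.91 v 5.22 | 29.1% | 0.499 v 0.500 |
| 8 | 0.4 | 7.14 v 6.60 | 6.7% | 6.84 v 6.01 | 23.3% | 0.575 v 0.596 |
| 8 | 0.7 | 8.32 v 7.73 | 5.1% | 7.87 v 6.86 | 21.7% | 0.641 v 0.699 |
| 12 | 0 | 7.94 v 7.33 | 7.6% | 6.99 v 6.05 | 35.0% | 0.499 v 0.500 |
| 12 | 0.4 | 9.33 v 8.63 | 6.8% | 8.03 v 6.86 | 32.6% | 0.620 v 0.650 |
| 12 | 0.7 | 10.96 v 10.15 | 4.2% | 9.07 v 7.57 | 36.1% | 0.748 v 0.807 |

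When stay is shortened for everyone alike, the recorded mean is shorter in the device arm in all nine rows. Kaplan-Meier censored at exit is unbiased when r = 0. At r = 0.4 or 0.7 it is too high in both arms, and more so in the device arm, by 0.016 to 0.059. The two planned analyses can then point in opposite directions.

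**Step 3: does the direction hold?** Three variations, again with no true effect:

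- *Stay cut by 40% only in patients who recover faster than the median.* The recorded mean becomes longer in the device arm, from 4.46 v 4.62 up to 8.29 v 10.43 days. If the cut falls only on slower patients, it becomes shorter, from 4.44 v 3.71 up to 8.34 v 5.82 days.
- *Patients without an in-ICU milestone ranked worst.* In those same scenarios the device arm always looks slower (probability that a device patient ranks slower: 0.52 to 0.60).
- *Early milestone (median 1 day, r = 0.4, stay 10 v 8 days).* About 99% v 97% have a value, and the means are 1.34 v 1.32 days.

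**The case against.** How patients without an in-ICU milestone are handled is commonly settled in an analysis plan, and none is shown. That stands for the handling rule. It does not stand for the window, which the article itself fixes: "Primary and secondary outcomes will be measured across the protocol duration". No later analysis rule can recover ward dates that were not collected.

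The Kaplan-Meier curves mean that the t-test would not stand alone. True, but they are complementary, and they are unbiased only if exit is unrelated to recovery, which is doubtful for ICU discharge.

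The limits of scope are disclosed: "The study does not assess successful rehabilitation of the patient subsequent to their intensive care unit stay". This restrains a reading about recovery after the ICU. It does not address the cut-off of times that are still compared between arms.

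The illustration rests on assumed stays and milestone times. The protocol's examples are simple bedside acts that many patients may manage before leaving. The protocol nowhere states that the device is expected to shorten ICU stay: its hypothesis concerns extubation. On recorded times alone the type I error was only 4% to 9%. All of this stands, and it limits the size of the point.

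A reader might infer something stronger: that the arm discharged sooner must record shorter times, so that the device will seem to speed recovery. The documents do not support this. Step 3 shows that the sign depends on who leaves early, on how patients without a milestone are treated and on how often the milestone precedes exit. The first and third are unknown, and the article does not state the second.

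**Conclusion.** The point holds as a possible bias of unknown direction. The article fixes a window that ends at ICU exit or death and names a test on times seen only within it. With identical recovery and an assumed 10 v 8 day stay, the recorded mean differed by 0.3 to 0.8 days in the log-normal scenarios and by up to 0.95 days in the closed form. Entering exit as the end time raised the type I error to 10% to 36%. Other equally plausible assumptions reverse the sign or make the difference negligible. First mobilisation is less exposed if it usually happens early in the stay; regained independence is probably more exposed.

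This concerns one secondary outcome among many. The primary outcome and the sample size are not affected.

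**What to change.** For both milestones, replace the test on recorded times with an analysis of all randomised patients: cumulative incidence of the milestone in ICU, with ICU exit without the milestone and death as competing events. Report it beside the cumulative incidence of ICU exit, and describe it as in-ICU attainment, not speed of recovery. The label matters. In step 1 with m = 6, attainment is 62% v 57% although recovery is identical, so this analysis describes what happened in the ICU and does not isolate recovery.

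Alternatively, for regained independence, report only the number of patients who reached it before ICU exit, without a test of mean times.

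If ward dates are readily available, collecting them for every patient to a common fixed horizon from randomisation (for example day 28) would be an optional improvement. It goes beyond the declared scope and would need data from every site, including for transferred patients.

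The main fix uses dates already collected for length of stay and mortality. It costs slightly more analysis work and a narrower interpretation of one secondary outcome.

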
### Statistical considerations

Sample size was determined by a power analysis of duration of mechanical ventilation. Extrapolation of the 2016 ICU admission data from two London-based NHS hospitals provided a sample size of 548 patients over an 18-month period. In these patients, mean total duration of mechanical ventilation measured in days was 7.2, with an SD of 7.0 days. A study population of 137 patients in each randomisation group would allow detection of a 2 day or 30% improvement in the duration of mechanical ventilation in the BEACON Caresystem group assuming a similar improvement in SD, with an α level of 0.05 and power of 0.8. A 2 days or 30% reduction in duration of mechanical ventilation is similar to that used previously.^6^

Primary and secondary outcomes will be measured across the protocol duration and comparison made by independent samples t-test, or appropriate non-parametric testing if not normally distributed. Complementary analysis will be performed using Kaplan-Meier curves.

The study is not sufficiently powered to allow subgroup analysis for the groups specified in the randomisation strategy.

An independent data safety monitoring committee will be established as part of the study, with this committee responsible for defining stopping criteria. Safety data will be looked at after the first 80 patients have been recruited, with an interim analysis performed following 50% recruitment.

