**Methods and analysis:**

Intenive Care weaning (iCareWean) is a single-blinded, multicentre, prospective randomised control trial evaluating management of mechanical ventilation as directed by the BEACON Caresystem compared with that of current care, in the general intensive care setting. The trial will enrol 274 participants across multiple London National Health Service ICUs. The trial will use a primary outcome of duration of mechanical ventilation until successful extubation.

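### One sample size and one power are given for two different effects: 137 per arm gives about 77% power for 2 days and 84% for 30%, before any loss of evaluable patients

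*Protocol article*

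**What the plan says.** The section Statistical considerations of the protocol article takes its inputs from local 2016 admissions, in which "mean total duration of mechanical ventilation measured in days was 7.2, with an SD of 7.0 days". It then states that "A study population of 137 patients in each randomisation group would allow detection of a 2 day or 30% improvement", "assuming a similar improvement in SD, with an α level of 0.05 and power of 0.8". The abstract gives the total: "The trial will enrol 274 participants across multiple London National Health Service ICUs", which is 2 × 137.

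The primary outcome (Primary and secondary outcomes) runs from the start of ventilation to successful extubation, which requires at least 48 hours of unassisted breathing. Follow-up ends at transfer or discharge from the ICU, or at death (end of the section on the spontaneous breathing trial). The planned analysis is a "comparison made by independent samples t-test, or appropriate non-parametric testing if not normally distributed", with Kaplan-Meier curves as a complement. The Discussion acknowledges that the trial was powered on total ventilation duration, because that was the historical variable available.

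**The concern.** The sentence treats 2 days and 30% as the same target. On a mean of 7.2 days they are not, and the stated power lies between the powers of the two. A reader who takes 2 days as the target will credit the trial with more power than it has.

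Two further features affect how far 0.8 can be relied on. The endpoint cannot be observed in a patient who dies before successful extubation, yet the enrolled total equals the computed total with no stated margin. And the calculation assumes a smaller SD in the intervention arm, which lowers the required number considerably.

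At stake is the reading of a null result. It would be judged against 80% power to detect 2 days, which the design does not quite have even with every patient evaluable.

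**Working it through.** **Inputs.** From Statistical considerations: control mean 7.2 and SD 7.0 days, effect 2 days or 30%, alpha 0.05, power 0.8, 137 per arm. Two-sided testing is my assumption, since sidedness is not stated. Loss rates are also assumed, since the article gives none.

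**Formulas.** Standard error `SE = sqrt((s1² + s2²)/n)`; noncentrality `δ/SE`; power from the noncentral t with Welch degrees of freedom. Normal approximation for size: `n = (s1² + s2²)(1.960 + 0.842)²/δ²`, where (1.960 + 0.842)² ≈ 7.849.

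**1. The two effects.** 2/7.2 = 27.8%. 0.30 × 7.2 = 2.16 days. A proportional fall takes the intervention SD to 7.0 × (1 − 2/7.2) = 5.06 for 2 days and to 7.0 × 0.70 = 4.9 for 30%.

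**2. Reproducing 137 (normal approximation).**
- 2 days, SD 7.0/5.06: (49 + 25.56) × 7.849/4 = 146.3, so 147.
- 2 days, SD 7.0/4.9: (49 + 24.01) × 7.849/4 = 143.3, so 144.
- 2 days, both SDs replaced by their average of 5.95: 2 × 35.40 × 7.849/4 = 138.9, so 139.
- 30%, SD 7.0/4.9: 73.01 × 7.849/4.666 = 122.8, so 123.

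The stated 137 is therefore approached but not hit by either named effect as written. It results exactly from about 2.05 days with SD 7.0/4.9. It also results from the 30% case with an unstated 10% inflation (122.8/0.9 = 136.5, so 137). A one-sided test does not explain it: with proportional SDs the t-based sizes are then 116 (2 days) and 98 (30%).

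**3. Power at 137 per arm (Welch t, two-sided).**

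| Effect | SDs | SE | δ/SE | Power | n per arm for 80% |
|---|---|---|---|---|---|
| 2 days | 7.0/5.06 | 0.738 | 2.711 | 77% | 148 |
| 2 days | 7.0/4.9 | 0.730 | 2.740 | 78% | 145 |
| 30% (2.16 days) | 7.0/4.9 | 0.730 | 2.959 | 84% | 124 |

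With the SD falling in proportion, 137 per arm reaches 80% power at about 2.07 days (28.7%).

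**4. Loss of evaluable patients (rates assumed).**

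| Loss | Evaluable per arm | Power, 2 days (SD 7.0/5.06) | Power, 30% (SD 7.0/4.9) |
|---|---|---|---|
| 10% | 123.3 | 72.6% | 79.8% |
| 20% | 109.6 | 67.5% | 75.0% |
| 30% | 95.9 | 61.6% | 69.2% |

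**5. SD unchanged.** With 7.0 in both arms, SE = sqrt(98/137) = 0.846. Power is 65% for 2 days (194 per arm needed for 80%) and 72% for 30% (166 needed).

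**The case against.** The strongest reply is that the sentence gives one rounded target. The 2.07 days that 137 per arm detects rounds to 2 days and, at 28.7%, is loosely 30%. The stated 0.8 lies inside the 77–84% range, an averaged SD gives 79% for 2 days, and the 30% reading gives more power than claimed. This stands in part. A reader might infer that 137 per arm simply fails to give 0.8 power; the document does not support that. The shortfall is about 3 points, and for the 2-day effect only. The imprecision remains, because the two named effects need sizes that differ by 24 per arm (148 against 124).

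On losses, it can be said that no death rate is given, that the handling of deaths may sit in an analysis plan not shown, that Kaplan-Meier curves can retain such patients, and that data collected before withdrawal are kept. The 137 may even contain a silent 10% margin on the 30% effect. All this is fair, so the loss figures are conditional and not a forecast. But the article presents 137 as the number giving 0.8, mentions no margin, and makes a comparison that needs a duration for each patient the main analysis.

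The shrinking SD is an assumption stated openly, so it is not an error. It is a sensitivity that the reader should see.

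A reader might also infer from "with an interim analysis performed following 50% recruitment" that the 0.05 level is left unprotected. The document does not support that either. Stopping criteria are assigned to the independent committee, no efficacy test at 0.05 is described for that look, and a boundary may sit in a charter or analysis plan.

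**Conclusion.** The point holds as an imprecise power statement with a modest error for one of its two effects. Under a two-sided 0.05 Welch test with the SD falling in proportion, and with every patient evaluable, 137 per arm has about 77% power for 2 days and about 84% for 30%.

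Losses matter more than the rounding. At 10% loss the surplus under the 30% reading is used up, and at 20–30% both readings are below 0.8. The size of that effect rests on assumed rates and on such patients contributing no value to the main comparison. The assumed fall in SD also matters more than the rounding: without it, power is 65% or 72% before any loss. The documents support no conclusion about the type I error of the interim analysis.

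**What to change.** Name one target effect and one intervention-arm SD, and state whether the test is two-sided. Then restate the power along these lines: *137 per arm gives 84% power for a 30% reduction (2.16 days, SD 7.0 and 4.9) and 77% for a 2-day reduction (SD 7.0 and 5.06), before loss of patients who are never successfully extubated.* Beside it, give the values for 10, 20 and 30% loss and for an unchanged SD of 7.0 as sensitivity figures. If 137 already includes a margin for loss, say so and give the rate.

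This is a change of wording. It needs no extra patients, and its cost is a less favourable stated power.

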### Primary and secondary outcomes

The primary outcomes include:

Duration of mechanical ventilation to successful extubation defined as the time from the start of mechanical ventilation, defined as either the time of intubation in the ICU, or the time of admission to the ICU following previous intubation for surgery, and until successful extubation, with successful extubation defined as ≥48 hours of unassisted spontaneous breathing after extubation.

Unassisted spontaneous breathing is defined here to include supplementary oxygen and support with high-flow nasal catheters. Patients with non-invasive mask ventilation are considered to be assisted.

The secondary objectives of the trial are to compare the following variables in the standard care group and BEACON Caresystem group:

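### The primary t-test or rank test has no value for patients who die or leave the ICU ventilated; if they are dropped or their time ends at death, the result can favour the arm with more deaths

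*Protocol article*

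**What the plan says.** Protocol article, Primary and secondary outcomes: the primary duration starts at intubation in the ICU (or at ICU admission after intubation for surgery) and runs "until successful extubation, with successful extubation defined as ≥48 hours of unassisted spontaneous breathing after extubation". No other end point of the clock is given.

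Section on the spontaneous breathing trial: "The protocol ends with transfer or discharge from ICU or death". The Discussion adds: "The study is not powered to detect changes in mortality, and does not follow-up on the patients after transfer from the ICU".

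Statistical considerations: outcomes are measured over the protocol duration and the "comparison made by independent samples t-test, or appropriate non-parametric testing if not normally distributed". The next sentence reads: "Complementary analysis will be performed using Kaplan-Meier curves". Neither sentence says how a patient without a successful extubation enters the comparison. The same section sizes the trial at 137 per arm for a 2-day difference at 80% power.

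Deaths are collected as a separate secondary outcome: "ICU mortality defined as the mortality from randomisation and until death or ICU discharge".

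**The concern.** A t-test or rank test on durations needs one number, or at least one rank, per patient. As defined, the primary outcome supplies none for anyone who dies on the ventilator or leaves the ICU still ventilated. All participants have had at least 24 hours of invasive ventilation in intensive care, so such patients are to be expected.

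This is more than a detail left to an analysis plan. The article names the test, and that test does not fit the outcome that it defines. The two simplest ways of running a t-test are to drop these patients or to treat time to death as the duration. The first compares only those who survived to extubation, a group formed after randomisation. The second counts a death as an end of ventilation like any other. Either way, a device that raised mortality without helping anyone off the ventilator could show a shorter mean duration, and a device that prevented deaths could show a longer one.

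**Working it through.** **The plan's own figure.** Inputs from Statistical considerations: control mean 7.2 and SD 7.0 days, difference 2 days, SD 30% lower with the device (0.7 × 7.0 = 4.9), α 0.05 (taken as two-sided), power 0.80.

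- Averaged SD (7.0 + 4.9)/2 = 5.95: n = 2 × 5.95² × (1.96 + 0.8416)² / 2² = 138.9, so 139 per arm.
- Separate SDs: n = (7.0² + 4.9²) × (1.96 + 0.8416)² / 2² = 143.3 per arm. Power at 137 per arm is 78.2%.

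The stated 137 is close to both and is not in dispute. It does assume that all 137 supply a value. If 10, 20 or 30% per arm have none and are dropped (123, 110 or 96 left), power for 2 days falls to 74, 69 or 63%.

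**Size of the distortion.** Assumptions, since the article gives no mortality: constant hazards, extubation e = 0.10/day in both arms (no true effect), death d = 0.04/day in control and 0.06 or 0.08/day with the device.

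- Share dying before extubation = d/(d + e): 0.04/0.14 = 28.6%; 0.06/0.16 = 37.5%; 0.08/0.18 = 44.4%.
- Among extubated patients, time is exponential with mean and SD 1/(d + e): 7.14, 6.25 and 5.56 days. The control value of 7.14 is close to the plan's 7.2 and 7.0.
- False benefit: 7.14 − 6.25 = 0.89 days; 7.14 − 5.56 = 1.59 days (from unrounded means).
- If the clock stops at death, the mean has the same formula, but all 137 per arm count, so the same false difference is estimated more precisely.

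Chance that the t-test significantly favours the device, by normal approximation Φ(difference/SE − 1.96) and by simulation at 137 per arm:

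| Device death hazard | Handling | SE (days) | Approximation | Simulation |
|---|---|---|---|---|
| 0.06 | dropped (98 v 86 patients) | √(7.14²/97.9 + 6.25²/85.6) = 0.99 | 14% | 14% |
| 0.08 | dropped (98 v 76 patients) | √(7.14²/97.9 + 5.56²/76.1) = 0.96 | 38% | 34% |
| 0.06 | clock stops at death | √((7.14² + 6.25²)/137) = 0.81 | 20% | 20% |
| 0.08 | clock stops at death | √((7.14² + 5.56²)/137) = 0.77 | 54% | 52% |

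The nominal rate in this direction is 2.5%. Repeat simulations agree to within a few percentage points.

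**Where the bias does not arise.** With deaths independent of extubation time (28.6% v 44.4%) and dropped, the t-test favours the higher-mortality arm in about 2 to 3% of trials, which is nominal. With early independent deaths (20% v 35%), it is 3% if they are dropped but 19% if the clock stops at death.

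**Analyses that keep everyone.** In simulations of early independent deaths, ongoing deaths, and ongoing deaths concentrated in sicker patients, a log-rank comparison that keeps dead patients at risk as never extubated favoured the higher-mortality arm in 0% of trials. Censoring at death gave 2.5 to 6.8%. A worst-rank test under the hazards in the table favoured that arm in under 1%.

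**Power of the worst-rank alternative** (survivors' mean 7.14 to 5.15 days):

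| Deaths, control v device | Worst-rank | t-test, survivors | Rank test, survivors |
|---|---|---|---|
| 28.6% v 20.6% (extubation hazard × 1.54; 0.04/0.194) | 71% | 65% | 53% |
| 28.6% v 28.6% | 21% | 61% | 49% |

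Its apparent advantage in the first row comes from the accompanying fall in deaths.

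**The case against.** A reader might infer that the plan as written rewards the arm with more deaths. The document does not support that. It states neither of the two handling rules, and its wording admits a non-parametric test, under which deaths could be ranked worst; that reverses the direction. A rule may also exist in an analysis plan not shown. Even when deaths are dropped, the direction depends on when and in whom they occur. All of this stands, and it limits the point to a conditional one.

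The other safeguards are also real. ICU mortality is a listed outcome, an independent safety committee is planned, and safety is reviewed after 80 patients. In the 0.08/day scenario, a chi-square test on deaths would detect the harm in 78% of trials. A false t-test benefit without a significant mortality signal would occur in about 8%, and at 0.06/day in about 9%. That reduces the risk of being misled, but both figures still exceed 2.5%, and the article says that it is not powered for mortality.

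The objection does not remove the mismatch. The article permits the rank test only where the data are not normal, not as a way of including deaths. The Kaplan-Meier curves can carry incomplete times, but they are complementary and have no stated rule for death.

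**Conclusion.** The concern holds in conditional form. From the article's own text, the primary outcome exists only for patients who are successfully extubated, follow-up ends at death or ICU exit, and the named primary test cannot use a patient without a value. Whether the result is then biased, and in which direction, depends on a rule that the article does not give. Under the assumed constant hazards, dropping deaths or stopping the clock at death raises the chance of a false benefit from 2.5% to roughly 14 to 34% or 20 to 52%. If deaths are independent of extubation time and dropped, it stays nominal. The mismatch itself is certain; the percentages rest on mortality and hazard assumptions and only illustrate its possible size. The point matters because it governs the confirmatory comparison. It does not show that the figure of 137 per arm is wrong.

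**What to change.** In Statistical considerations, replace the primary test with an analysis of all 274 randomised patients. One suitable choice is time to successful extubation with death as a competing event: compare the cumulative incidence of successful extubation, keeping patients who die as never extubated. State in the same place how a patient who leaves the ICU still ventilated is counted. Report deaths by arm beside the primary result, since a lower incidence of extubation can reflect more deaths. Keep mean days among extubated patients as description only.

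A Wilcoxon test with deaths ranked worst is an alternative, but it should not be chosen on the ground that it has more power: its power ranges from about 71% to about 21% according to whether deaths also fall.

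No new data are needed, because deaths are already an outcome and ICU exit already ends the protocol. There are two costs. The primary result is no longer a difference in mean days. The stated 80% power must also be re-expressed for the new analysis, with an explicit mortality assumption; that power has not been calculated here for the competing-event analysis.
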